#### Activity level and return to sport

The level of knee-demanding physical activity will be assessed using the Tegner Activity Scale (TAS) which evaluates activity level on a 0–10 scale, where 0=sick leave or disability pension because of knee problems and 10=participation in knee-demanding competitive sports, such as soccer, football or rugby, at a national or international elite level. The TAS is valid, reliable and responsive to changes in populations with knee injuries including ACL tears (online supplemental table 1). Return to sport will be assessed by comparing participants’ post-injury TAS score to their pre-injury TAS score. Only participants who were active at TAS ≥6 pre-injury will be considered eligible for the return-to-sport analysis. For these participants, we will then assess whether they have indicated returning to level 6 or above on the TAS, and whether the sport they are back to is the same as the one they indicated participating in before their injury on their initial questionnaire.

#### Reinjuries and further surgery

The incidence of subsequent/recurrent injuries to the index knee or contralateral knee will be recorded by asking participants to report all future knee injuries to either knee since enrolment, including the specific diagnosis (if known), whether they subsequently underwent surgery and if so, the type and timing of the surgery.

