### Participants

Australian residents of any age who have sustained a traumatic knee injury in the previous 6 months are eligible. A traumatic knee injury is defined as a knee injury of sudden onset that is severe enough to interrupt daily life, work, school and/or sport activities for more than 24 hours, resulting in contact with the healthcare system (eg, for imaging, diagnosis and/or management). Australian residents are defined as those living in Australia at the time of their knee injury and throughout most of their healthcare pathway. The aim is to recruit at least 1000 participants.

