### Data collection procedure

Data will be collected at baseline (on initial enrolment in the study) and at 6 months, 1, 2, 5 and 10 years after the initial injury. For each follow-up, participants will receive an email with a link to the online questionnaire. To support retention and address potential issues, such as participants changing their email addresses during the study, reminders will be sent via email, phone call and text message. Informed by our consumer advisory group (CAG), data collection will be kept to a minimum at each time point (less than 5–10 min) to minimise participant burden and encourage retention. For this reason, some questionnaires include only specific subscales and single-item scores for certain constructs (online supplemental table 1) provides detailed information about the questionnaires. If any questionnaire is incomplete or further clarification is required regarding participant responses, a member of the research team will telephone participants to follow-up or seek clarification.

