### Outcomes

#### Baseline demographic, injury characteristics and outcome expectations

Demographic characteristics will include age, sex, gender and current residential postcode. The postcode will be used to classify geographic location (eg, metropolitan vs regional, state of residence) using the Australian Statistical Geography Standard and infer socioeconomic status (via linkage with the Socio-Economic Indexes for Areas index). Details regarding current knee injury will include the involved side (index knee), the Australian state and setting (eg, sport, work, other) where the injury occurred, diagnosis and how it was confirmed (eg, self-reported, clinician-diagnosed or imaging-confirmed), as well as the patient’s patient preference for management options. For those who have not undergone post-injury surgery at baseline, management preference will be assessed with the question ‘If you were asked right now to choose surgery or rehabilitation without surgery, which option would most accurately represent your answer?’ with five response options ranging from ‘Strong preference for surgery’ to ‘Strong preference for rehabilitation without surgery’. In addition to self-report, knee injury diagnosis will be confirmed via imaging reports (if imaging has been performed) from clinical services. With participant consent, a member of the research team will contact the clinic or imaging provider where the participant reported having their imaging performed, to request a copy of the report. Information about prior knee injuries (eg, side involved, diagnosis) will also be recorded. Participants’ recovery expectations will also be assessed with the question ‘Overall, how do you expect your knee to be 1 year after your injury?*’* with responses recorded on a 7-point Likert scale (range: 1=very much worse, 7=completely recovered) which corresponds to the Global Rating of Change scale used to assess self-perceived change in knee status (table 1).

**Table 1 T1:** Overview of outcomes

	Baseline	6 months	1 year	2 years	5 years	10 years
Demographic and knee injury characteristics						
Age, sex, gender, postcode	√					
Current and prior knee injury details	√					
Recovery expectations	√					
Self-reported outcomes						
Healthcare pathway Private insurance cover and how treatment was paid for Healthcare provider seen, sequence and timing Referral patterns Imaging acquisition Surgical procedures Rehabilitation participation		√	√			

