Patient acceptable symptom state	√	√	√	√	√	√
Health-related quality of life (EQ-5D-5L)	√	√	√	√	√	√
Mental health (100-point VAS)	√	√	√	√	√	√
Knee pain (100-point VAS)	√	√	√	√	√	√
Knee instability (100-point VAS)	√	√	√	√	√	√
Activity level (TAS)	√	√	√	√	√	√
New/reinjury occurrence and details		√	√	√	√	√
Global rating of change		√	√	√	√	√
Function in sport and recreation (KOOS-Sport/Rec)		√	√	√	√	√
Knee-related quality of life (KOOS-QoL)		√	√	√	√	√
Fear of reinjury (100-point VAS)		√	√	√	√	√
Surgery occurrence and details				√	√	√

KOOS, Knee injury and Osteoarthritis Outcome Score; TAS, Tegner Activity Scale; VAS, visual analogue scale.

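### The reinjury question starts at enrolment while follow-up is timed from injury, so new injuries in a gap of 0 to 6 months fall outside it

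*Protocol article*

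**What the plan says.** Under Participants, the article states that residents who "have sustained a traumatic knee injury in the previous 6 months are eligible". Enrolment can therefore fall anywhere from 0 to 6 months after the index injury. Under Data collection procedure, baseline takes place at enrolment, and follow-up questionnaires are sent "at 6 months, 1, 2, 5 and 10 years after the initial injury".

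Under Reinjuries and further surgery, the incidence of later injuries to either knee is to be recorded by "asking participants to report all future knee injuries to either knee since enrolment". The details of each event that the section names are given in a list that covers diagnosis and any surgery, and no date of the new injury appears in it: "including the specific diagnosis (if known), whether they subsequently underwent surgery and if so, the type and timing of the surgery". In Table 1 the row "New/reinjury occurrence and details" is ticked at 6 months and at 1, 2, 5 and 10 years. It is not ticked at baseline.

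One baseline item touches on other injuries: "Information about prior knee injuries (eg, side involved, diagnosis) will also be recorded".

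**The concern.** Two time origins are in use. The visits run on a clock that starts at the index injury; the reinjury window starts at enrolment, at a point that differs between participants. An event in between belongs to neither the reinjury question nor, on a natural reading, the injury history before the index injury.

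At stake are the early reinjury figures. If reinjury is later reported by time since injury, as the visit schedule invites, the 6-month and 1-year figures would combine people observed for nearly the whole period with people observed for little or none of it, and would be too low. This is a matter of data collection. An analysis plan can correct the denominator, but it cannot restore events that nobody was asked about.

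**Working it through.** The article states no reinjury rate, no distribution of enrolment delay and no sample-size calculation, so there is no figure of its own to reproduce. The check is arithmetic on the stated windows.

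**Inputs**
- Gap g between index injury and enrolment: 0 to 6 months (Participants).
- Visit times T since injury: 6, 12, 24, 60 and 120 months (Data collection procedure).
- Start of the reinjury window: enrolment (Reinjuries and further surgery).

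**Formula.** Unobserved share of time since injury = g / T.

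| Gap g | 6 months | 1 year | 2 years | 5 years | 10 years |
|---|---|---|---|---|---|
| 1 month | 16.7% | 8.3% | 4.2% | 1.7% | 0.8% |
| 3 months | 50% | 25% | 12.5% | 5% | 2.5% |
| 6 months (maximum) | 100% | 50% | 25% | 10% | 5% |

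For example, 3/12 = 25% and 6/60 = 10%. A participant who enrols at 6 months has no reinjury window at all before the 6-month visit.

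**Averages over participants.** These need an assumed distribution of g. Because g / T is linear in g, only the mean delay matters. Enrolment spread evenly over 0 to 6 months has a mean of 3 months, which gives the middle row. Enrolment concentrated early, with a mean of 1.5 months, gives half of that row: 1.5/6 = 25%, 1.5/12 = 12.5%, 1.5/24 = 6.25%, 1.5/60 = 2.5% and 1.5/120 = 1.25%.

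**From lost time to lost events.** This needs a reinjury rate, which the article does not give. Assume a constant hazard r, so that the first-event risk falling in the gap is 1 − exp(−r·g), with g in years. For the maximum gap of 0.5 years:
- r = 2% per year: 1 − exp(−0.010) = 1.0 percentage points
- r = 5% per year: 1 − exp(−0.025) = 2.5 percentage points
- r = 10% per year: 1 − exp(−0.050) = 4.9 percentage points

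As a share of the full risk 1 − exp(−r·T), this is about 50% to 51% at 1 year but only 5.5% to 7.7% at 10 years. The proportion lost is thus large early and small late across the assumed rates.

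**Effect of moving the origin.** With the window starting at the index injury, g is 0 and the unobserved share is 0% at every visit for every participant.

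**The case against.** The strongest reply has four parts.

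*The gap may be partly covered.* The baseline item on earlier knee injuries is not expressly limited to injuries before the index one, and a second injury before enrolment might itself be entered as the qualifying injury. Surgery in the gap can appear in the healthcare-pathway items at 6 months and 1 year, though not labelled as following a reinjury. This stands as far as it goes: a reader might infer that gap injuries are captured nowhere, and the article does not establish that. Nor does it say that any of these items is meant to capture them.

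*The sentence is a description, not questionnaire wording.* Several other items are given verbatim; this one is not. A reader might infer that each of the five follow-ups reuses the same window, that no injury date is collected, and that repeat reports of one event cannot be told apart. The article does not support these inferences. The wording could describe the combined coverage of successive questionnaires, the list of details is introduced as a partial one, and Table 1 refers to unspecified details. Side, diagnosis, surgery timing, earlier answers under the same participant number and telephone clarification would allow at least partial matching. What remains is that duplicates may be hard to separate when no surgery followed, if no date is recorded.

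*Reinjury incidence is not one of the three aims, and delayed entry deals with the gap.* Both statements are right. Reinjury is one outcome among many, no reporting of incidence at a given visit is promised, and counting person-time from enrolment can give valid post-enrolment rates. That still leaves the period before enrolment undescribed.

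*Differential loss is conjecture.* This also stands. No section gives enrolment timing by management group. The loss could differ between surgical and non-surgical participants if their enrolment timing does, and no more can be said.

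**Conclusion.** The mismatch of time origins is in the text: the stated reinjury window leaves out 0 to 6 months after the index injury, by an amount that varies between participants. It matters for reinjury figures at 6 months and 1 year, less at 2 years, and little at the horizons that the article calls long-term, where the loss is at most 10% (5 years) and 5% (10 years) of the time since injury. The maxima follow from the eligibility window alone. The typical values rest on an assumed mean delay of 1.5 to 3 months, and the event losses on assumed constant hazards. The long-term comparisons are not undermined. This is a cheap improvement to data collection, worth making while recruitment is open, which the article says is until 2027.

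**What to change.** - At the first completed follow-up, ask for new injuries to either knee since the index injury, with its date shown.
- At later follow-ups, ask for new injuries since the last completed questionnaire, with its date shown.
- Record the month, year and side of each new injury. This places events in time and limits duplicate reports.
- For participants who have already answered the enrolment-anchored item, count person-time from enrolment (delayed entry), and do not present their figures as observed from injury.
- State in the protocol whether the baseline item on earlier knee injuries is meant to include injuries between the index injury and enrolment.

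The cost is a text edit in REDCap with inserted dates, a date field per new injury if there is none yet, and slightly longer recall at the first follow-up.

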#### Global rating of change

Self-perceived change in knee status from the time of injury will be assessed with the question ‘Overall, how would you rate your knee compared with when you first injured it?’*.* Responses will be recorded on a 7-point Likert scale ranging from 1 (very much worse) to 7 (completely recovered).

#### Knee-related function in sport/recreation and quality of life

Participants will complete two subscales of the Knee injury and Osteoarthritis Outcome Score (KOOS): (1) knee-related function in sport and recreation and (2) knee-related quality of life. Our CAG identified these specific subscales as the most important ones, as they are particularly relevant and responsive in populations of young, active adults with knee injuries. Each subscale consists of 4 items, rated on a 5-point Likert scale (ranging from ‘no problems’ to ‘extreme problems’). Item scores are summed, transformed and presented as a score from 0 to 100, where 0 indicates extreme problems and 100 indicates no problems. The overall KOOS has good psychometric properties and both subscales are valid in knee-injured populations. They have high test–retest reliability (online supplemental table 1). They are commonly used in clinical practice and research to monitor sports and recreational function, as well as knee-related quality of life, after injury.

#### Fear of reinjury

Fear of knee reinjury will be assessed with a single item from the ACL-QoL questionnaire: ‘How fearful are you of re-injuring your knee?’*.* Responses will be recorded on a 100-point VAS (where 0=no fear at all and 100=extremely fearful).

### Sample size calculation

No sample size has been calculated for the cohort; however, we aim for a minimum of 1000 participants. An important element of this study is understanding the extent of knee injuries in Australia, and we will include as many participants as possible during the active recruitment period. If appropriate, the required sample size will be calculated for specific research questions to ensure the analyses conducted are sufficiently powered. If the necessary resources are available, recruitment may extend beyond the expected endpoint of December 2027. This will facilitate the creation of a larger database, enabling the exploration of additional research questions, the evaluation of quality control markers, model-based budget impact analyses or economic evaluations, and the conduct of real-world target trial emulation studies.^28^

### Statistical analyses

Since this nationwide cohort will provide data over multiple years (up to 10-year follow-up) and cover a range of constructs (eg, demographics, injury and treatment characteristics, healthcare pathway, knee function, quality of life, mental health, return to sport), multiple analyses are planned. Specific statistical analysis plans will be developed for each research question, and these will be refined over time with the input from the relevant personnel. Broadly, descriptive statistics will be used to describe participant demographics, injury characteristics and the healthcare pathway. Regression analysis and other statistical methods will be applied to determine the impact of participant baseline characteristics on management strategy (ie, surgical vs non-surgical) and long-term outcomes, as well as the impact of healthcare pathway and management strategy on long-term outcomes. More specifically, for the three main aims:

Descriptive statistics and visualisation methods (eg, Sankey diagrams) will be used to map and summarise healthcare pathways. The use of latent class cluster analyses will also be considered if healthcare pathways are found to be heterogeneous. Knee injury types (eg, ACL, meniscal, MCL tears) will be reported separately, allowing for targeted analyses based on injury type.Multivariable logistic and multinomial regression models will be used to identify patient- and healthcare-related predictors of management strategy (ie, surgical vs non-surgical).Long-term outcomes across injury types and management strategy will be evaluated using linear and generalised linear models, adjusted for relevant confounders and baseline characteristics.

To evaluate the representativeness and generalisability of the study, we will compare the baseline characteristics (eg, age, sex/gender, injury type) of KIICS participants with those of other national injury registries and available Australian population data. We will also monitor and report the number of each injury (eg, ACL, meniscal, etc.) identified during the study recruitment period and assess the demographic characteristics (age, sex/gender) of this group to evaluate any potential recruitment bias. These steps will allow us to determine how our cohort sample compares to the broader population of Australians with traumatic knee injuries.

### Data management

All data will be collected and managed via REDCap web-based software (hosted at La Trobe University), facilitating simultaneous data entry. For data analysis, personal data, including participant names, contact details, date of birth and imaging reports, will be securely stored on the La Trobe University server Research Drive Storage, separately from deidentified (numbered) data. All subsequent study data will be identified by participant number only. Participants will be informed that, if they choose to withdraw from the study, their personal health information already collected will be retained, unless an explicit request to the contrary is made, to ensure that the results of the research project can be properly assessed.

### Patient and public involvement

A CAG comprising eight individuals (mean±SD age: 27±7 years; 5 women and 3 men) with lived experience of an acute knee injury (ACL and/or meniscal tear) was involved in the co-design of this study. This CAG was established using the Patient Engagement in Research framework^29^ and drawing on the experience from other CAGs established within our research centre.^30^ Experienced clinicians were also consulted regarding recruitment strategies and relevant outcomes to include. Ongoing CAG consultation will continue to influence recruitment strategies, research questions of importance and the overall acceptability of the study. Consultation meetings with the CAG will be planned to occur 2–4 times per year to provide insights and feedback on study documentation (eg, recruitment material and strategies) as well as relevant research questions and data interpretation. Members of the CAG have received financial compensation for their time spent contributing to the study design and will continue to receive compensation for their time in future meetings.

## Discussion

The healthcare pathways used by patients following traumatic knee injuries remain poorly understood, and the factors (eg, patient- and healthcare-related) influencing management strategy (surgical vs non-surgical) are not well documented in Australia. While evidence from RCTs supports non-surgical management for some people with ACL and meniscal tears, there is a need for complementary real-world longitudinal data to support decision-making in clinical practice. This study will be the first nationwide study in Australia to address these knowledge gaps by identifying key factors (patient- and healthcare-related) influencing healthcare pathways and management strategies after a traumatic knee injury. It will also explore the long-term patient-reported outcomes associated with different injury types and management strategies and examine potential disparities related to sex/gender, pre-injury activity level and access to care (eg, geographical remoteness, socioeconomic status).

To our knowledge, this is the first study to comprehensively map healthcare trajectories following acute knee injuries, encompassing both surgical and non-surgical management. The study design was developed with input from a multidisciplinary group of experienced clinicians and researchers, as well as a CAG comprising individuals with lived experience of acute knee injury. Consumer and community involvement led to several design decisions aimed at reducing participant burden, such as using short questionnaires and lay language instructions to simplify the reporting of healthcare pathways. As a result, the study employs single-item questions in some instances instead of full-length, validated patient-reported outcome measures (eg, using a single VAS item rather than the full Kessler Psychological Distress Scale for mental health, and only selected KOOS subscales are used). This approach prioritises feasibility, but we recognise that it may reduce the granularity and comprehensiveness of certain constructs, such as mental health. The fully online, self-reported design introduces potential recall bias, participant attrition and selection bias, as some patients with acute knee injuries may not be included.

## Data Availability

No data are available.
